#### Sample Size and Power

Demonstrating efficacy of the intervention through detection of a statistically significant effect size was not a primary goal of the project. However, we considered it plausible that the intervention might significantly influence participants’ decisions to receive HCV testing even after a single session. While planning the pilot trial, we calculated a target sample size that would be sufficient to detect what we considered to be a meaningful difference in the proportion of participants who undergo HCV testing within 12 months after enrollment. Assuming that approximately 10% of participants would be known to have HCV infection at enrollment and accounting for expected losses to follow-up, we estimated that a sample size of 408 would provide 90% power to detect a difference of 0.15 in the proportion of participants who voluntarily returned for an HCV test within a year of enrollment.

We believed that achieving a target sample size of 408 was feasible and justified based on data from the pilot survey conducted in 2012 reporting that 69.4% of syringe exchange clients had an HCV test in the prior 12 months and 14.9% of clients had ever had a positive HCV test [1]. Because this intervention was targeting people who inject drugs but may not be regular users of the syringe exchange program, we anticipated that the number reporting prior HCV testing would be lower. We believed an effect size of this magnitude was reasonable based on prior meta-analyses of tailored communication interventions, which provide support for moderate mean intervention effect sizes [20] across a variety of health behaviors, including addiction-related behaviors (eg, smoking) and HIV risk-related behaviors [37]. Notably, findings suggested effect sizes increased with the number of behaviors intervened upon, with mean effect size of g=.24 (95% CI 0.18-0.31) for interventions focused on 3 behaviors [20].

#### Data Analysis

Descriptive statistics reported here were calculated for baseline variables using SAS 9.3 (SAS Institute Inc). Differences in participant characteristics were assessed using a Wilcoxon rank-based general linear model approach for continuous variables and Pearson chi-square or Fisher exact tests for differences in categorical variables.

To evaluate the effectiveness of the risk reduction intervention, we will test within-group changes from baseline to follow-up (eg, change in frequency of needle-sharing) using the matched-pair Wilcoxon rank-sum test. Similarly, binary outcome changes will be examined using either the McNemar test or Fisher exact test.

To assess the independent role of the intervention in improving screening for HCV, we will use a logistic regression model on the binary outcome of having an HCV test within the 12-month period postintervention. Again, a Wilcoxon general linear model framework will be used for analysis of Likert scale outcome measures. Indicators pertaining to individual level outcomes within intervention and control groups will be measured among the same individuals at baseline and follow-up.

To avoid potential sampling bias toward individuals with larger networks, we will adjust regression models using inverse probability weights based on individual recruitment network sizes [33]. To account for correlation between recruiter and recruited, we will create a variable indicating who the recruiter of each subject was and use it as a cluster variable using generalized estimating equations. An exchangeable correlation structure within each cluster will be assumed (ie, correlation between any 2 subjects recruited by the same recruiter will be assumed to be the same). For all tests, a 2-sided *P* value of less than .05 is considered statistically significant.

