#### Randomization

After completion of all required sections of the baseline survey, participants were randomly assigned to receive the risk reduction intervention or be in the control group, in which the computer session terminated after completion of the survey. Both the intervention and control groups received individualized prevention counseling per standard of care at the syringe exchange programs. Challenges related to data synchronization across multiple sites and the need for offline data collection in rural communities made stratified, block randomization infeasible. Therefore, simple randomization was used to place participants to either group using the survey software during the baseline session.

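### Effectiveness on self-reported injection and drug-use behaviour is to be tested by before/after change within groups, with no between-arm contrast stated for these outcomes

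*Protocol article*

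**What the plan says.** The Data Analysis section of the protocol article sets out three strands.

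- **Behaviour change.** "To evaluate the effectiveness of the risk reduction intervention, we will test within-group changes from baseline to follow-up". The example given is needle-sharing frequency, "using the matched-pair Wilcoxon rank-sum test". For yes/no items: "Similarly, binary outcome changes will be examined using either the McNemar test or Fisher exact test".
- **HCV testing.** To isolate the role of the intervention, "we will use a logistic regression model on the binary outcome of having an HCV test within the 12-month period postintervention".
- **Likert items.** "a Wilcoxon general linear model framework will be used for analysis of Likert scale outcome measures". The text does not say whether arm is a term in this model.

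The section adds: "Indicators pertaining to individual level outcomes within intervention and control groups will be measured among the same individuals at baseline and follow-up". The data for the first strand are therefore paired and exist in both arms. Regression models are to carry weights for recruitment network size, and generalized estimating equations (GEE) are to handle clustering by recruiter. The significance level is two-sided .05.

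On the control condition, the Randomization section says: "Both the intervention and control groups received individualized prevention counseling per standard of care at the syringe exchange programs". The Baseline Study Assessment section applies the same computerised questionnaire, and the same encouragement to take a rapid HCV test, to all participants.

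**The concern.** The question a randomised trial answers is whether the arms differ. A test of change within one arm asks whether that arm differs from its own past, and everything else that happened between the two visits is part of the answer.

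Here several things happen to both arms: counselling, a long risk questionnaire and the offer of an HCV test. Eligibility also required injection in the past 30 days. That behaviour is present in everyone at baseline and can only fall.

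Testing each arm separately and setting the two P values side by side does not repair this. Significance in one arm and not in the other is not a test of the difference.

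At stake is the interpretation of the self-reported behavioural outcomes. The article's Conclusion ties wider dissemination to confirmation of the study hypotheses.

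A smaller matter is that two of the named tests do not suit paired data. Rank-sum and Fisher exact are tests for independent samples.

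**Working it through.** The article gives no operating figure for the within-group tests, so there is none to reproduce. Its sample size of 408 concerns HCV testing and does not bear on this point.

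**Inputs from the article**
- Arm sizes: control 126, intervention 109 (Table 2).
- Sharing in the past 3 months: 71 of the 161 who had ever shared, out of 234 with data (Results). Those who never shared count as no, so the baseline rate is 71/234 = 30.3%.
- Injection in the past 30 days: 100% at baseline, by eligibility.
- Two-sided .05.

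**Assumptions not in the article**
- An equal fall in sharing to 20% in both arms, so the intervention effect is zero.
- Within-person latent correlation 0.5 or 0.7.
- Follow-up of 100% (109/126) or 80% (87/101).
- Independent participants.

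**Check 1: recent sharing.** Each person's baseline and follow-up status is a bivariate normal pair cut at 30.3% and 20%. Within an arm, exact McNemar is P = 2 × Pr(Bin(b+c, 0.5) ≤ min(b, c)), capped at 1, where b is the number who stop and c the number who start. The between-arm test is a two-proportion z test on follow-up status. There were 6,000 simulated trials per row.

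| Latent correlation | Follow-up | Intervention arm significant | Significant in intervention arm only | Between-arm test |
|---|---|---|---|---|
| 0.5 | 100% | 47% | 20% | 5% |
| 0.5 | 80% | 38% | 21% | 5% |
| 0.7 | 100% | 58% | 20% | 5% |
| 0.7 | 80% | 48% | 22% | 5% |

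A separate model let a fixed share of sharers stop and 5% of non-sharers start, equally in both arms, at full follow-up. The intervention arm was significant in 27%, 58%, 79% and 92% of trials as sharing fell to 24.7%, 21.7%, 18.7% and 15.6%. The between-arm test stayed at 4 to 6%. With no change in sharing, the within-arm McNemar test rejected in about 1%. The problem therefore arises from change common to both arms.

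**Check 2: past-30-day injection.** No one can start, so c = 0 and P = 2 × 0.5^b. Five stoppers give 0.0625 and six give 0.031, so six are enough. If each person stops with probability 5% for any reason, Pr(Bin(109, 0.05) ≥ 6) = 46%. For the control arm, Pr(Bin(126, 0.05) ≥ 6) = 61%. At 10% stopping, the intervention arm is significant with probability 97%. At 70% follow-up (76 people) and 5% stopping, it is 18%.

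**Check 3: the test names.** In simulation at n = 109 with no change, an unpaired rank-sum test on paired data rejects 2.2%, 0.5% and 0.03% of the time at correlations 0.3, 0.5 and 0.7. Signed-rank rejects about 4 to 6%. With sharing falling from 30.3% to 21.7%, Fisher exact rejects in 17% of trials and McNemar in 58%. The misnamed tests err on the conservative side, so the false attribution comes from the within-group comparison.

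**The case against.** The strongest reply is that this is a pilot. The Sample Size and Power section says that showing efficacy through a significant effect was not a primary goal, and feasibility and acceptability come first. HCV testing, the outcome behind the sample size, has its own regression. The Follow-Up Assessments section already warns that self-reported drug use may be biased. All of this stands and lowers the severity. It does not make a within-group test a test of effectiveness, which is the purpose the article gives it.

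A second reply is that a condensed article leaves detail to an analysis plan that is not shown. That holds for detail. Here the article names a method and a purpose, and the two do not match.

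Some stronger readings are tempting, but the article does not support them.

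- *The randomised comparison is abandoned for three of the four target behaviours.* The Likert model may compare arms, and attitude, norm and self-efficacy items were written for each target behaviour. The gap is established only for self-reported injection and drug-use behaviours.
- *Only returners will be analysed.* The article does not say so, and missing-data handling commonly sits in the analysis plan.
- *The wrong test names produce false positives.* They are conservative. The words matched-pair suggest that rank-sum is a slip for signed-rank, and McNemar is named first.
- *Regression to the mean drives the sharing result.* Entry selected on recent injection, not on sharing.

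The simulated sizes depend on assumed changes. They also ignore correlation within referral chains, although 195 of the 235 participants were referred by peers.

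**Conclusion.** The point holds for self-reported injection and drug-use behaviours. The stated test of effectiveness is change within a group, and no between-arm contrast is given for them. It does not extend to 12-month HCV testing, and it may not extend to the Likert items.

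Under an assumed common fall in sharing from 30.3% to 20%, with latent correlation 0.5 to 0.7 and 80 to 100% follow-up, a useless intervention yields a significant intervention-arm change in about 38 to 58% of trials. A between-arm test does so in about 5%. For past-30-day injection, an assumed 5% stopping rate gives about 46% at full follow-up. The exact values move with the assumptions, and without any common change the excess disappears.

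A reader might infer that such a change will be reported as an intervention effect. The article does not establish that, because the authors could show both arms together. It establishes only that the stated test cannot tell the two explanations apart. Should-fix.

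**What to change.** Replace the sentence on within-group testing with a between-arm comparison of the follow-up value, adjusted for the baseline value of the same item.

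- Use logistic regression for binary items and a rank-based or ordinal model for frequency items. For past-30-day injection, baseline is the same for everyone and drops out.
- Fit these within the GEE recruiter clustering and network-size weights that the Data Analysis section already specifies.
- Report the arm difference with its 95% CI.
- State whether arm is a term in the Likert model.
- Keep within-arm change as description only. If it is tested, use Wilcoxon signed-rank (correcting rank-sum) and McNemar, and drop Fisher exact for paired data.

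The cost is a few sentences of analysis wording and modest programming. The items are collected at baseline and follow-up in both arms, so no new data are needed.

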Finally, Internet connectivity and a private space to screen and deliver the survey were difficult barriers to overcome. Neither syringe exchange program had readily available WiFi, so Ethernet accessibility was imperative in collecting and synchronizing survey data. Private spaces with Ethernet accessibility were difficult to keep consistently vacant of other prevention services, which made data collection more difficult. Furthermore, a substantial number of study assessments were completed via mobile syringe exchange outreach where no Internet connectivity was available. The remote data collection feature in the DatStat software package was used for these surveys, which added a layer of complexity causing some frustration among participants and staff.

The main limitation of this study is its lack of generalizability to other cities and states and other local epidemics. While Hep-Net may be feasibly used in the context of Wisconsin’s opioid epidemic, it may not apply to other geographical areas targeting the same population. This CTI used existing preliminary data from a pilot study of over 500 Wisconsinites to tailor the intervention content to a specific population. Additionally, our sample was subject to selection bias because individuals using a syringe exchange program tend to be a healthier, higher-functioning subset of people who inject drugs. Although the computerized approach to data collection was designed for complete anonymity to reduce social desirability bias, participants may have answered questions to please researchers.

A major strength of this study is the use of well-established syringe exchange programs as home to Hep-Net. The community-based prevention specialists who implemented this project are highly regarded among community members and have built trust over years of service. Without their involvement, acceptability of the intervention would likely have been much lower.

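### The 12-month HCV-testing model is valid as described, but its stated adjustments leave out baseline HCV testing information that could sharpen the arm comparison

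*Protocol article*

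**What the plan says.** All references are to the protocol article.

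- **Randomization:** "Therefore, simple randomization was used to place participants to either group using the survey software during the baseline session". The reason given is that data synchronisation across sites and "the need for offline data collection in rural communities made stratified, block randomization infeasible". No intended stratification factor is named.
- **Unanticipated Challenges:** "a substantial number of study assessments were completed via mobile syringe exchange outreach where no Internet connectivity was available". The share is not given.
- **Data Analysis:** the model for 12-month testing is introduced with the words "To assess the independent role of the intervention in improving screening for HCV", and the sentence continues "we will use a logistic regression model on the binary outcome of having an HCV test within the 12-month period postintervention". Two adjustments follow: "we will adjust regression models using inverse probability weights based on individual recruitment network sizes", and a variable for each participant's recruiter, where the plan is to "use it as a cluster variable using generalized estimating equations". No baseline covariate is named, and none is ruled out.
- **Sample Size and Power:** 408 participants for 90% power to detect a difference of 0.15 in 12-month testing, assuming that about 10% would already be known to have HCV.
- **Results:** 235 enrolled (126 control, 109 intervention). Tables 2 and 3 have no row for testing history, HCV status, baseline rapid-test uptake, site or delivery setting.

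**The concern.** Stratified allocation was not feasible, so balance on factors that predict later testing was left to chance. Regression on baseline factors is the usual way to recover some of the lost precision, but the two adjustments stated do other jobs: the weights address who was sampled, and the clustering addresses correlation between people with the same recruiter. Neither uses a participant's own testing background.

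The article gives reason to think that this background bears on whether a further test is sought. The Baseline Study Assessment section says that people with a past positive antibody test, or a rapid test in the last 3 months, were not urged to test. In Results, 36 of 155 decliners cited previous testing and 17 of 155 known positivity. The sample-size section itself allows for people already known to be infected.

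At stake is the width of the confidence interval in a trial that enrolled 235 of a planned 408.

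**Working it through.** **1. The plan's own figure.** The 408 cannot be reproduced uniquely, because neither the control rate nor the loss rate is stated. Two readings come close:

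- 69.4% v 84.4% needs 164 per arm; 164/(0.9 × 0.9) = 202.5, so 203 per arm or 406 in total (10% known infected, and an assumed 10% loss).
- 20% v 35% needs 370 in total, or 412 after a 10% inflation alone.

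Nothing below depends on which was used.

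**2. Power at the enrolled size.** Take 40% v 55% (assumed), with 126 and 109.

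- 1/126 + 1/109 = 0.01711
- Unpooled SE = sqrt(0.24/126 + 0.2475/109) = 0.0646
- Pooled rate = (50.4 + 59.95)/235 = 0.4696, so pooled SE = sqrt(0.4696 × 0.5304 × 0.01711) = 0.0653
- Power = Φ[(0.15 − 1.96 × 0.0653)/0.0646] = 0.63

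Across control rates of 20% to 69.4% the same formula gives about 63% to 78%.

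**3. Chance imbalance.** For a factor with prevalence q, the SD of the arm difference is sqrt(q(1 − q) × 0.01711).

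| q | SD | P(difference above 10 points) |
|---|---|---|
| 0.50 | 0.065 | 0.126 |
| 0.34 (baseline rapid test, 80/235) | 0.062 | 0.107 |

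The shift in the risk difference is imbalance × effect of the factor on testing.

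- A 10-point imbalance with an assumed 30-point effect gives 0.10 × 0.30 = 0.03, one fifth of 0.15.
- At q = 0.5 the 95% range of imbalance is ±12.8 points. With effects of 20, 30 and 40 points the shift is at most 0.026, 0.038 and 0.051.

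**4. Gain from adjusting.** Simulation: 235 participants, simple 1:1 allocation, one 50%-prevalence predictor, control rates of 30%, 42.5% and 50%, 8,000 runs per cell, no clustering or weights.

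| Effect of predictor on testing | Power without it | Power with it | Gain (points) |
|---|---|---|---|
| 20 points | 63.4–67.1% | 65.1–68.7% | 1.6–2.0 |
| 30 points | 63.9–66.4% | 67.6–71.0% | 3.7–4.7 |
| 40 points | 62.9–65.5% | 70.6–74.1% | 7.7–8.6 |

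With no true effect, type I error was 4.4–5.4% without the predictor and 4.5–5.4% with it. The mean unadjusted difference was within 0.002 of zero.

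**5. Cross-check by hand.** The predictor removes a share g²q(1 − q)/v of the outcome variance. Here g is its effect and v = (0.24 + 0.2475)/2 = 0.244.

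- For q = 0.5 and g = 0.2, 0.3, 0.4 the shares are 4.1%, 9.2% and 16.4%.
- The standardised effect 0.15/0.0646 = 2.32 becomes 2.37, 2.44 and 2.54.
- Power, Φ(effect − 1.96), goes from 64.1% to 65.9%, 68.3% and 71.9%: gains of 1.8, 4.2 and 7.8 points.

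**6. Less favourable prevalence.** The 50% figure is the best case. For known or newly found HCV positivity, the 17 decliners who knew they were positive and the 14 reactive tests do not overlap, so q is at least 31/235 = 13.2%. The same formula with g = 0.4 then gives a share of 7.5% and power of 67.5%, a gain of 3.4 points.

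**7. Are these baseline values?** Yes. The fingerstick came before the survey, and randomisation after the required survey sections, so the specimen and the choice to test both precede allocation. Testing history was collected: Results reports that 49 of 161 equipment sharers had never been tested.

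**The case against.** The strongest reply is that nothing here is wrong. Simple randomisation with an arm-only logistic model is a valid analysis. An article may leave its covariate list to an analysis plan that is not shown, and speaking of an independent role of the intervention may well mean that covariates are intended. That stands: the article does not say that the model is unadjusted. What remains is that its Data Analysis section is specific about weights, cluster variable and correlation structure, but silent on the one group of baseline measures most closely tied to the outcome.

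A reader might infer that chance imbalance biases the arm contrast. It does not: it is random error that the standard error already counts. Even the 0.03 shift is under half a standard error, which at 40% testing is sqrt(0.24 × 0.01711) = 0.064.

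A reader might also infer that site or delivery setting is a strong predictor that must be adjusted for. The article does not show this. The move to drop-in appointments was made at both sites, the municipality figures describe residence rather than place of enrolment, and the account of mobile outreach concerns connectivity, not access to tests.

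Two further points stand. No association between any baseline factor and 12-month testing is reported. Baseline rapid-test uptake is also a mixed signal, since decliners include the previously tested, the not ready and the known positive; it is best used together with history and status, not alone. Finally, showing efficacy was not a primary goal of this pilot.

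**Conclusion.** The point holds as a minor efficiency improvement. The model described is valid: no bias and no inflation of type I error. It gives up some precision by not stating the use of testing and infection information fixed before allocation. The cost is about 2 to 9 points of power if a factor held by half the sample shifts testing by 20 to 40 points, and less if the factor is weaker or rarer. Those effect sizes are assumptions, and the simulation ignored weights and clustering, so the figures show order of magnitude only. The reported absence of significant baseline differences does not settle balance on these factors, because they are not among those tabulated. The documents do not support calling this a flaw in randomisation or in the validity of the comparison.

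**What to change.** State in Data Analysis, or in the analysis plan before the 12-month testing data are examined, that the model includes besides arm:

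- self-reported HCV testing before baseline;
- known HCV-positive status at enrolment, counting a reactive baseline rapid test (not needed if such participants are excluded from this outcome);
- rapid test taken at the baseline encounter (yes/no).

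Add exchange site or setting only if it is recorded for each participant.

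Covariates change what the odds ratio measures, so also report a standardised risk difference: predict each participant's probability under both arms, average, and subtract, with a standard error that respects the recruiter clustering. It is then comparable with the 0.15 in Sample Size and Power.

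The cost is a short addition to the plan and a few degrees of freedom. The testing items are already collected; whether setting is held per participant needs checking.

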## Methods

### Study Design

#### The Hep-Net Intervention: Overall Objectives

This project has two main objectives. First, it aims to determine whether a CTI is a feasible and acceptable approach to increasing readiness to engage in various health-promoting behaviors among people who inject drugs. It targets 4 different behavioral domains: (1) undergoing regular HCV screening, (2) using clean works for every injection, (3) taking steps to prevent opioid overdose, and (4) reducing and ultimately ceasing injection drug use. The second objective is to determine the feasibility of using social networks to expand delivery of computerized prevention interventions to hard-to-reach people who inject drugs.

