#### Baseline Study Assessment

At the initial study encounter, participants were encouraged to get a rapid HCV antibody test unless they had had a positive HCV antibody test in the past or had gotten a rapid HCV test within the last 3 months. Receiving an HCV test was not a requirement for participation in the study; it is a standard service offered to all syringe exchange clients. The computerized survey was designed to last 20 to 30 minutes. For those consenting to HCV testing, the baseline assessment was administered after participants provided a fingerstick blood specimen for the rapid HCV test, allowing them time to complete most of the baseline assessment while awaiting the test results. The complete baseline questionnaire is reproduced in Multimedia Appendix 1.

Question items were developed based on the integrative model to evaluate attitudes, norms, and self-efficacy beliefs relevant to each of the targeted health behaviors. Table 1 displays sample question items assessing the relevant constructs in the integrative model for the behavior of HCV testing. Response options to each of these questions were a 5-point Likert scale ranging from “strongly disagree” to “strongly agree.” Participants rated their readiness to make changes toward each of 4 behavioral goals: (1) “I will cut down on my drug use or quit using drugs completely,” (2) “I will use clean needles, cottons, and cookers every time I inject drugs,” (3) “I will get tested for hepatitis C every 6 months for as long as I’m using,” and (4) “I will get trained to give naloxone (or Narcan) in case someone I am with has an overdose.”

**Table 1 table1:** Examples of questions based on the integrative model.

Survey question	Integrated model domain
“I am confident that if I really wanted to, I could get tested for hepatitis C every six months, for as long as I am shooting drugs.”	Self-efficacy
“Most people who are important to me think I should get tested for hepatitis C.”	Injunctive normative beliefs
“Most people who are similar to me have been tested for hepatitis C.”	Descriptive normative beliefs
“Getting tested for hepatitis C is important to me.”	Attitudes

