#### Follow-Up Assessments and Outcome Measures

Upon completion of the baseline session, participants were reminded of the need to return for a follow-up assessment 3 months after the baseline session. The second study visit uses an Internet-based survey designed to assess the same behavioral and attitudinal domains captured through the baseline questionnaire. This allows us to evaluate any temporal changes in the frequency of substance use, injection risk behaviors, overdose risk, and HCV testing. The follow-up assessment also evaluates self-reported readiness to change, attitudes, and perceived norms, providing an opportunity to detect whether the tailored intervention may influence outcomes through these intermediate variables.

In addition to repeating the assessment of baseline variables for longitudinal analysis, the follow-up questionnaire captures information on participant perceptions about whether they met any of the health goals discussed in the baseline session. For participants determined to be HCV-infected at baseline, the survey assesses whether they received any follow-up testing or medical care for HCV since receiving their test result. Finally, it evaluates usability and acceptability of the intervention through a series of questions delivered to participants who were randomized to the active study arm. The additional questionnaire items used during the follow-up assessment are presented in Multimedia Appendix 3.

There are multiple behavioral outcomes of interest in this project. Accurate assessment of drug use behaviors may be limited because it relies on participant self-report and may be biased due to losses to follow-up. HCV testing behavior may be captured with greater validity because it will be ascertained by searching HCV testing data collected and reported by all agencies receiving funding from the Wisconsin Division of Public Health. For participants who have received a reactive HCV screening test result, we will determine whether any follow-up testing was performed, including confirmatory HCV RNA or HCV genotype tests, which would indicated that the participant was linked to evaluation and/or treatment of HCV.

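### The rank-based model for the Likert outcomes does not state that each scale's pre-randomisation score enters the between-arm comparison, which may forgo a cheap, modest gain in precision

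*Protocol article*

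**What the plan says.** All places are in the Methods of the protocol article.

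- **Objective.** The first objective is given as follows: "determine whether a CTI is a feasible and acceptable approach to increasing readiness to engage in various health-promoting behaviors among people who inject drugs" (Overall Objectives).
- **Baseline.** Attitude, norm and self-efficacy items are answered on a 5-point Likert scale, and "Participants rated their readiness to make changes toward each of 4 behavioral goals" (Baseline Study Assessment). Readiness is scored on what the article calls a visual analog scale, by choosing a statement along the stages of change.
- **Timing.** The article reads, in part: "After completion of all required sections of the baseline survey, participants were randomly assigned to receive the risk reduction intervention or be in the control" (Randomization). The scores are therefore true pre-randomisation values. Allocation was by simple randomisation, without stratification or blocks.
- **Follow-up.** "The follow-up assessment also evaluates self-reported readiness to change, attitudes, and perceived norms", and baseline measures are repeated: "In addition to repeating the assessment of baseline variables for longitudinal analysis" (Follow-Up Assessments and Outcome Measures).
- **Analysis.** Data Analysis will "test within-group changes from baseline to follow-up (eg, change in frequency of needle-sharing) using the matched-pair Wilcoxon rank-sum test". For the Likert scales, "Again, a Wilcoxon general linear model framework will be used for analysis of Likert scale outcome measures", followed by "Indicators pertaining to individual level outcomes within intervention and control groups will be measured among the same individuals at baseline and follow-up". Regression models are adjusted by inverse probability weights for network size, and clustering by recruiter is handled by generalized estimating equations with an exchangeable correlation.

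**The concern.** Data Analysis is specific about weights, cluster variable, working correlation and alpha, yet it gives no baseline term for the comparison of arms on these scales. The sentence opens by referring back to the approach used for comparing participant characteristics at baseline, where no covariate is named either. A natural reading is an unadjusted comparison of the arms at follow-up.

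A person's baseline score on a scale usually predicts the follow-up score on that scale, so leaving it out leaves explainable variance in the error term. That matters more here because the sample is small: the target fell from 408 to 120 per group, and 126 and 109 were enrolled. Losses to follow-up are also expected. The covariate is already in the data set.

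Three analyses fit the text: follow-up score alone, change score, or follow-up score with baseline as a covariate. They differ in power, so the choice should be stated.

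**Working it through.** **The plan's own figure.** There is none to reproduce. The only sample size, 408, concerns HCV testing within 12 months; no power is stated for the scales.

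**Inputs from the article.** Arm sizes 126 and 109 (Table 2). Two-sided alpha .05 (Data Analysis). Effect 0.24 SD, borrowed from the g=.24 in Sample Size and Power. That figure is cited there for tailored interventions across health behaviours, not for these scales, so its use here is an assumption.

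**Assumed inputs.** The correlation ρ between baseline and follow-up is not given; the range is 0.3 to 0.7. Retention is not given; 100%, 80% and 60% are shown. Weights and clustering are ignored.

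**Formulas.** With outcome SD 1, SE = √[v(1/126 + 1/109)], where

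- follow-up only: v = 1
- baseline as covariate: v = 1 − ρ²
- change score: v = 2(1 − ρ)

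Power = Φ(0.24/SE − 1.96) + Φ(−0.24/SE − 1.96); the second term is negligible.

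**Numbers.** 1/126 + 1/109 = 0.01711, so SE = 0.1308 for follow-up only, and 0.24/0.1308 = 1.835. Power = Φ(−0.125) = 45.0%. At ρ = 0.5, SE = 0.1308 × √0.75 = 0.1133, the ratio is 2.119, and power = Φ(0.159) = 56.3%.

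| ρ | 1 − ρ² | Follow-up only | Baseline as covariate | Change score |
|---|---|---|---|---|
| 0.3 | 0.91 | 45.0% | 48.5% | 34.1% |
| 0.5 | 0.75 | 45.0% | 56.3% | 45.0% |
| 0.7 | 0.51 | 45.0% | 72.9% | 65.9% |

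The covariate's gain equals that from 1/(1 − ρ²) − 1 more participants: 10%, 33% and 96%. A change score beats follow-up alone only when 2(1 − ρ) < 1, that is ρ > 0.5, and it never beats the covariate.

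**With losses.** At 80% retention, 37.5% becomes 40.5%, 47.4% or 63.2% for ρ of 0.3, 0.5 or 0.7. At 60% retention, 29.5% becomes 31.9%, 37.5% or 51.2%.

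**Check on a 5-point item.** A latent normal score was cut into five categories and analysed by a linear model on ranks, with and without ranked baseline (3000 runs, full retention). Monte Carlo error is about 0.9 points, from √(0.41 × 0.59/3000).

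| ρ | Follow-up only | Ranked baseline as covariate | Ranked change |
|---|---|---|---|
| 0.3 | 40.7% | 43.3% | 29.0% |
| 0.5 | 41.0% | 49.1% | 38.6% |
| 0.7 | 42.4% | 63.3% | 54.1% |

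With no effect, the first two analyses rejected in 5.1% to 5.7% of runs.

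**The case against.** **The text is silent; it does not exclude baseline.** A general linear model can carry a baseline covariate. The next sentence stresses that the same people are measured twice, and the repeat measures are said to serve longitudinal analysis. A journal article may also leave covariates to the full plan. This stands as far as it goes: a reader might infer that baseline is definitely not used, and the article does not say so. What remains is that the section lists its other adjustments in detail, assigns baseline only to within-group tests (which do not compare the arms), and leaves open analyses that differ in power.

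**Readiness may not be covered.** The quoted sentence concerns Likert outcomes, while readiness is described as a visual analog stage scale. This stands. A reader might conclude that the trial's first-named target loses power, but that is not established. No other between-arm model is named for readiness, so the article should say which applies. The point holds for the attitude, norm and self-efficacy items regardless.

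**Efficacy was not a primary goal.** Sample Size and Power says so. The first objective concerns feasibility and acceptability, and the follow-up section treats readiness, attitudes and norms as intermediate variables. This stands and limits the importance.

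**Simple randomisation could leave baseline readiness unbalanced.** A reader might call this a bias. It is not: the unadjusted contrast is unbiased in expectation, and its interval already allows for chance imbalance. No imbalance on these scales is shown. The cost is in precision only.

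**The size is not anchored in the article.** Both ρ and the effect are assumed. Weights and clustering would generally lower the effective sample size in either analysis. The figures are illustrative.

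**Conclusion.** The point holds in a limited form. The article does not state that each scale's pre-randomisation score enters the between-arm rank-based model. Run as written, without it, the model gives up precision on the attitude, norm and self-efficacy items, and on readiness if the same model is meant there.

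Under the assumptions above with full retention, the gain is about 3 to 4 points of power at ρ = 0.3, 11 at 0.5 and 28 at 0.7. On a simulated 5-point item it is about 3, 8 and 21 points. If a change score was intended, the normal-theory gain from using the covariate instead is about 14, 11 and 7 points. If ρ is near 0.3, little is lost against a follow-up-only analysis.

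This is a worthwhile, modest improvement for intermediate outcomes of a pilot. The article does not support a claim of bias, of baseline having been ruled out, or of a failure of the primary objective.

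**What to change.** In Data Analysis, after the sentence on the Likert outcomes, add wording such as:

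> For each attitude, norm and self-efficacy scale, the intervention and control groups will be compared at follow-up in the rank-based linear model, with treatment arm and the ranked baseline score of the same scale as covariates. The planned network-size weights and recruiter clustering are kept. The same model applies to the readiness stage scale for each of the four goals.

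If another model is meant for readiness, name it instead. Use baseline as a covariate and not a change score, for the reason shown in the tables.

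**Cost.** One sentence, one degree of freedom per model, and no new data or participants. A simple rule is needed for missing baseline items, such as a simple imputation or a missing indicator. Some baseline items are incomplete: ethnicity in Table 2 is given for 112 + 12 = 124 of 126 controls. The article expected follow-up to run until March 2016, so when it was written the rule could still be fixed before the outcome data were complete.
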